Procedure / Visit (month (mo))	Enrollment	6 mo	12 mo	24 mo	30 mo
Seated blood pressure check	X	X	X	X	X
Diabetes mellitus screening (perform fasting blood glucose if any signs/symptoms suggestive of underlying diabetes)	X^*^	X	X	X	X
uACR^a^ (No urine protein testing necessary for enrolled Aim 2 HIV-positive adults with normoalbuminuria as all HIV-positive ART-treated adults from Aim 1 will have one uAPR measurement) (We will have stored urine at 3 timepoints to go back and perform uAPR testing in patients with incident microalbuminuria)	X^#^ (We will use Aim 1 uACR as participants baseline value)		X		X
Serum creatinine (SCr)^b^	X (We will use Aim 1 SCr as their baseline value)		X		X
Parasite screening					
Complete blood count (CBC) with differential^c^	X	X	X	X	X
Urine dipstick (spun for all patients with hematuria followed by urine microscopy (*S. haematobium*)	X	X	X	X	X
Malaria testing (rapid diagnostic test) at point-of-care (POC) using fingerprick specimen	X	X	X	X	X
Filariasis POC testing for *Wuchereria bancrofti*^d^	X				X
Onchocerciasis testing (bilateral skin snips)^e^	X				X
Stool for ova and parasite (stool O&P)^f^	X	X	X	X	X
Daytime thick blood smear for *Loa loa* (10 AM–2 PM)	X				X
Strongyloides IgG serology (plasma)^g^	X				X
Tuberculosis screening^h^	X	X	X	X	X
Inflammatory biomarkers (urine and plasma)^i^	X				X
CD4 cell count	X				X
Viral load (plasma HIV RNA)	X				X
Social and Behavioral data	X		X		X
Additional tubes for storage^j^	X		X		X

*All potentially eligible Aim 2 participants will undergo fasting blood glucose testing to evaluate for diabetes (and if ≥ 6.1

mmol/L (110 mg/dL), then patient may have diabetes, is ineligible, and is referred to medical provider/clinic for evaluation

^#^All participants will use their recent uACR measurement (obtained in Aim 1) for their baseline

^a^Two 3 mL sterile universal containers taken for uACR testing (Urine protein testing only for HIV-positives)

^b^Two 3 mL gold top tubes taken to measure serum creatinine (SCr)

^c^CBC with differential—looking for eosinophilia (common with Filariasis (especially *Loa loa*) and Schistosomiasis)

^d^POC testing for *W. bancrofti* antigen by Filariasis Test Strip (FTS), followed by obtaining nocturnal thick blood smears for

microfilaria [between 10 pm—2 am] in FTS-positive persons. *Brugia spp. *are not endemic to Africa, so testing for *W*

*bancrofti* will be sufficient

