#### *Adverse clinical outcomes* will be assessed at all study visits by trained study research staff

*Hospitalizations:* We will ask all participants if they have been hospitalized in the previous 6 months. If they answer affirmatively, we will ask the reason for hospitalization and approximate dates.*Death*: Ascertained from medical records or from a contact identified by the participant during consent.*Inflammation* will be assessed from plasma and urine specimens collected, as detailed in Table 6. Plasma inflammatory biomarker assay testing will be performed in duplicate at the DMPI Biomarker Core Facility using the Mesoscale Discovery Platform. Based on the literature, we chose a panel of plasma and urine biomarkers [92–101] that will help us elucidate the processed by which chronic inflammation contributes to albuminuria. Urine inflammatory/tubular injury biomarker assay testing will be performed at the [name] laboratory (Brigham and Women’s Hospital Biomarker Laboratory, Boston, MA, USA). Some are novel biomarkers whose role in clinical research is being defined.*Plasma inflammatory markers:* highly sensitive C-reactive protein (hsCRP), IL-6, soluble TNF-receptor 1 (TNFR-1), soluble TNF-receptor 2 (TNFR-2), IL-1β, and TNF (with biomarker levels of sCD14, fibrinogen, and possibly additional plasma biomarker levels to be ascertained pending additional funding/approved sub-studies).*Urine inflammatory/tubular injury biomarkers*: NGAL, KIM-1, and MCP-1 (with biomarker levels of IL-18, interferon-gamma inducible protein-10 (IP-10), and possibly additional urine biomarker levels to be ascertained pending additional funding/approved sub-studies).

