#### Statistical analysis plan

Demographic and clinical characteristics will be summarized by descriptive statistics. We will perform two sets of analyses: (1) categorizing uACR and investigating time from enrollment to albuminuria onset (first uACR measurement > 30 mg/g), and (2) keeping uACR as a continuous variable and investigating mean change in repeated uACR measures. Categorization of uACR is common in the literature and allows easy clinical interpretation, whereas continuous analysis tends to result in greater power. For (1), discrete-time proportional hazards models with a complementary log–log link will be fit. For (2), generalized estimating equations (GEE) with an identity link (i.e., linear model) will be fit to repeated measures of log_10_-transformed uACR. We will fit models limited to PWH, with cumulative TDF exposure as the primary (time-varying) exposure. The association between albuminuria and cumulative exposure to other regimens (e.g., protease inhibitors) will also be considered, both in models with and without cumulative TDF exposure. Analyses will adjust for viral suppression status. Secondary analyses will exclude the anticipated small proportion (< 5%) that will not be virally suppressed.

For hypothesis (ii), we will fit models with HIV status, hypertension, and an interaction between HIV status and hypertension. For hypothesis (iii), we will fit models with time-updated biomarkers of inflammation, both current and cumulative exposure. For inflammatory analyses, we will compute a composite inflammation score [102] for each participant that has been shown to accurately predict the phenotype of interest, based on levels (at least initially) of select markers, with a score of 1 being assigned to each individual biomarker measurement deemed “*high*” (or “*significantly elevated*”) delineated as follows: hsCRP > 3 mg/L, IL-6 > 6 pg/mL, TNF ≥ 7 pg/mL, and IL-1β ≥ 0.39 pg/mL. We will also perform analyses including inflammation biomarkers as continuous variables, both individually and in combination with other biomarkers.

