Urine and plasma biomarkers will be collected and stored on all Aim 2 study participants, but we will perform case–control analyses using cases defined as participants who develop incident albuminuria during follow-up (i.e., incident cases) and compare their biomarker profiles to a matched set of non-albuminuric controls. We conservatively estimate that we will observe ~ 130 incident cases; we plan to match three controls to each case based on age (± 10 years), sex, HIV-status, CD4 cell count at enrollment among those HIV-positive (within 50 cells/mm^3^), and hypertension status. If matching on this many factors proves to be difficult, then we will consider matching on the predicted probability of being a case based on the factors listed above (i.e., propensity score-type matching). We will account for the case-cohort nature of the design with appropriate analyses that account for outcome-dependent sampling [103].

All analyses will account for confounding variables, including time-updated viral suppression status (only participants with suppressed viral load will be enrolled), smoking status, BMI, CD4 cell count, age, exposure to TDF or protease inhibitors, etc. We anticipate using propensity score matching weights [104], to account for the high number of confounders, particularly in our time-to-albuminuria analyses (which will likely not have enough events to allow inclusion of all potential confounders). In all analyses, to relax linearity assumptions, continuous predictors will be expanded using restricted cubic splines.

Missing data, which we assume will be minimal, will be imputed using multiple imputation procedures. The longitudinal nature of our data collection may also permit investigation of mediation (e.g., hypertension → inflammation → albuminuria), which will be explored using relevant methods [105].

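### Aim 2 plans time-updated and cumulative inflammation biomarkers, but assays at enrolment and month 30 give no updated value before albuminuria onset

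*Protocol article*

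**What the plan says.** All references are to the Protocol article, Specific aim 2, unless stated.

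- **Exposure.** Statistical analysis plan: "For hypothesis (iii), we will fit models with time-updated biomarkers of inflammation, both current and cumulative exposure". This is the hypothesis lettered b) in the Background, that ongoing inflammation is associated with higher rates of albuminuria.
- **Outcome.** Same section: the first set of analyses is "investigating time from enrollment to albuminuria onset (first uACR measurement > 30 mg/g"), fitted with discrete-time proportional hazards models. The second set is a GEE on repeated log10 uACR.
- **Biomarker schedule.** In Table 6 the row "Inflammatory biomarkers (urine and plasma)^i" is marked at enrolment and 30 months and blank at 6, 12 and 24 months. The inflammation text adds no other time; it says inflammation "will be assessed from plasma and urine specimens collected, as detailed in Table 6".
- **uACR schedule.** Table 6 marks uACR at enrolment ("We will use Aim 1 uACR as participants baseline value"), 12 and 30 months. The clinical assessments text under Study measures instead has albuminuria assessed at every visit. The two conflict.
- **Stored samples.** The row "Additional tubes for storage^j" is marked at enrolment, 12 and 30 months. Its footnote reserves these tubes for future or approved testing. The one stated later use of urine stored at three time points is uAPR in incident cases.
- **Case-control comparison.** Cases are those with incident albuminuria. The plan will "compare their biomarker profiles to a matched set of non-albuminuric controls", without saying which visit supplies the profile.

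**The concern.** A time-updated exposure is useful in an incidence model only if the updates come before the event. Here the exposure and outcome schedules do not fit together: the single biomarker update falls at the last visit, so it can never precede an onset.

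The inference of Aim 2 is at stake. Aim 2 restricts entry to people with normal uACR so that exposures can be related to later albuminuria. A month-30 biomarker set against a month-30 albuminuria diagnosis is a cross-sectional comparison inside a longitudinal model. Kidney injury can raise some of these markers. The protocol itself describes NGAL, KIM-1 and MCP-1 as inflammatory or tubular injury biomarkers. A raised value at the outcome visit may be a consequence of the process that produced the albuminuria, and the analysis could not tell the two directions apart.

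**Working it through.** **Step 1: line up the schedules.** Biomarkers are taken at months {0, 30}. Each possible onset visit is checked under both readings of the uACR schedule.

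| uACR schedule | Onset detected at month | Biomarker before | Same visit | After |
|---|---|---|---|---|
| Table 6 (12, 30) | 12 | 0 | none | 30 |
| Table 6 (12, 30) | 30 | 0 | 30 | none |
| Every visit (6, 12, 24, 30) | 6, 12 or 24 | 0 | none | 30 |
| Every visit (6, 12, 24, 30) | 30 | 0 | 30 | none |

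The number of updated values before onset is zero in every row. The uACR conflict does not alter this, because month 30 is the last visit under both readings.

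**Step 2: what enters the discrete-time model.** In any interval ending before month 30, the latest available biomarker is the enrolment value. In the interval ending at month 30, the current value is the one taken at that visit. A single coefficient for the current biomarker would therefore mix a prospective association (enrolment value, later onset) with a same-visit association.

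**Step 3: the cumulative term.** The protocol gives no formula. As an illustration, a trapezoid over follow-up is 30 × (B0 + B30)/2, so half the weight falls on the value from the outcome visit. For a case detected earlier, the cumulative term can only be the enrolment value carried forward, unless a post-outcome value is used.

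**Step 4: how many cases are affected.** Inputs are from the Aim 2 sample size section: 1000 HIV-positive at 10% and 500 HIV-negative at 5.9%.

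- Expected cases: 1000 × 0.10 + 500 × 0.059 = 129.5, which reproduces the plan's figure of about 130.
- Assumption: constant hazard, with these incidences reached by month 30. (Table 7 labels them 3-year incidence; the match to 130 suggests that the plan applies them to the whole follow-up.)
- Table 6 schedule, detected at month 12: 1000 × (1 − 0.90^(12/30)) = 41.3 and 500 × (1 − 0.941^(12/30)) = 12.0, total 53.3. Detected at month 30: 129.5 − 53.3 = 76.2.
- Every-visit schedule, detected at month 30 only: 1000 × (0.90^(24/30) − 0.90) = 19.2 and 500 × (0.941^(24/30) − 0.941) = 5.8, total about 25.

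So between about 25 and 76 of some 130 cases would have a same-visit value as their only update. The rest have no usable update.

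**Step 5: other routes for the month-30 value.** The case-control comparison names no time point. If it used month-30 profiles, a month-12 case would contribute a value taken 30 − 12 = 18 months after detection.

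**Step 6: with month-12 assays added.** With biomarkers at {0, 12, 30}, a month-30 case has two earlier values (0 and 12), hence one true update. A month-12 case still has only the enrolment value beforehand.

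**The case against.** The strongest reply is that the plan retains a valid analysis. The enrolment biomarker precedes every incident case, and both the hazard model and the case-control comparison can use it. That stands, and the fix rests on it. Four further points limit the concern.

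- **Post-outcome values in the hazard model.** A reader might infer that this model would regress month-12 onset on a biomarker taken 18 months later. The documents do not support that: in a time-to-first-event model a month-12 case leaves the risk set and contributes no month-30 record. Cumulative exposure is likewise not undefined for every case; for earlier cases it reduces to the enrolment value.
- **The GEE.** It has no onset time. A concurrent association between month-30 biomarkers and month-30 uACR is a legitimate cross-sectional estimate, and the hypothesis is worded as an association.
- **Mediation.** A reader might infer that hypertension and biomarkers are first measured together, which would defeat the exploratory mediation work. They are not: blood pressure is taken at the Aim 1 visits (Tables 1 and 2), and dates of hypertension diagnosis are collected.
- **Sampling label.** The biomarker set is introduced as case-control, and then the plan says "We will account for the case-cohort nature of the design". This is a separate labelling matter, largely covered by the undertaking to allow for outcome-dependent sampling.

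Two other replies do not succeed. The stored month-12 tubes make a repair possible, but the article plans no biomarker assay on them. A separate analysis plan could choose a lag, but it cannot supply a measurement that the schedule omits. The injury-marker argument is weaker for the composite score, which uses only four plasma markers, but the lack of any update before onset applies to that score too.

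**Conclusion.** The point holds in limited form and should be corrected before the assays and models are run. The planned time-updated, current and cumulative biomarker terms cannot do what they are meant to do for incident albuminuria, because no case has an updated value before onset. This follows from the two schedules alone and needs no distributional assumption. The terms add only same-visit information, for roughly 25 to 76 of about 130 cases depending on which uACR schedule applies; those counts rest on a constant hazard and the plan's own incidences. For earlier cases, any use of the month-30 value, for instance in the case-control comparison, would be post-outcome. Reverse causation then cannot be excluded, especially for the urine tubular injury markers.

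A reader might conclude that the inflammation hypothesis is untestable in this study. The documents do not support that: analyses based on the enrolment biomarker remain sound, and the concurrent GEE association is valid if described as such.

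**What to change.** 1. In the hazard and case-control analyses, make the enrolment biomarker (continuous markers and composite score) the exposure for incident albuminuria. Remove the time-updated, current and cumulative wording there, and state that the case-control profiles are those at enrolment.
2. Keep month-30 biomarkers in the GEE as a concurrent, cross-sectional association with month-30 uACR, and label it so.
3. Optionally, assay the stored month-12 plasma and urine in the matched set and use them only as a lagged exposure for the month 12 to 30 interval.
4. Reconcile the uACR schedule between Table 6 and the clinical assessments text, and align the hypothesis labels: (iii) in the analysis plan, b) in the Background.

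Items 1, 2 and 4 cost wording only, unless reconciling the schedule adds uACR visits. Item 3 costs one assay run in up to 130 × (1 + 3) = 520 people and needs approval to use the stored tubes.

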Other factors that may contribute to albuminuria can be broken down into three main categories: i) *direct kidney injury* (i.e., exposure to the ARV medication TDF, which can cause tubulopathy); ii) *immune activation/inflammation* from HIV or specific viral pathogens (e.g.*, Cytomegalovirus* [CMV], hepatitis B or C) and/or other endemic co-infections (e.g., parasitic infestations, tuberculosis); and iii) *environmental factors/exposures* (*i.e*., traditional medications, heavy metals, etc.). This study will include an in-depth evaluation of direct kidney injury and immune activation/inflammation. Depending on results, future studies may evaluate potential environmental exposures.

Because R3 participants were ART-experienced, with the majority receiving TDF at some point in their course, another important research question is to determine whether albuminuria is *tubular* or *glomerular* in etiology. Tenofovir is an effective ARV medication, widely used in first-line ART regimens [24, 25]. Although data suggest that it is not universally associated with kidney toxicity [26–30], it can be associated with renal tubular dysfunction, including Fanconi syndrome [25, 30–33]. This is especially important in our study setting, where the alternative formulation of tenofovir, tenofovir alafenamide (TAF), which has a more favorable bone and kidney toxicity profile, is not routinely available.

Despite improved patient survival with ART [34, 35], non-AIDS defining conditions such as cardiovascular and kidney disease and non-AIDS-defining malignancies are more prevalent among ART-treated HIV-positive than HIV-negative adults [34, 36–39]. While factors such as smoking and ARV-related toxicity explain some of the increased risk for these events [34, 40], excess immune activation, inflammation, and poor immune restoration [34, 41–51] have also been shown to predict disease. Chronic immune activation and inflammation are hallmarks of HIV infection. [34, 51, 52]

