### Statistical considerations

#### Sample size

We will enroll 1500 (1000 HIV-positive and 500 HIV-negative) patients with normoalbuminuria and follow them for up to 30 months. Table 7 summarizes differences in albuminuria incidence that we will have 80% power to detect between the HIV-positive and HIV-negative groups, over a range of sample sizes and albuminuria incidence rates in the HIV-positive group. We will have approximately 80% power to detect a difference of developing albuminuria of 10% (HIV-positive) vs. 5.9% (HIV-negative), or a relative risk of about 1.70 (Bold emphasis row in Table 7).

**Table 7 Tab7:** Detectable alternative for various rates of developing albuminuria for the HIV-positive adult patients

HIV-positive adults, N	HIV-negative adults, N	3-year incidence of albuminuria for HIV-positive adults	3-year incidence of albuminuria, HIV-negative adults, 80% power to detect	Relative Risk
1000	500	5%	2.2%	2.28
**1000**	**500**	**10%**	**5.9%**	**1.70**
1000	500	15%	10.0%	1.51

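### Aim 2's single covariate list for all analyses puts TDF/PI exposure, viral suppression and CD4 into the HIV-positive versus HIV-negative contrast, so the adjusted HIV effect is not the one Table 7 is powered for

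*Protocol article*

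**What the plan says.** The Aim 2 statistical analysis plan sets one general rule: "All analyses will account for confounding variables, including time-updated viral suppression status". The list goes on with "smoking status, BMI, CD4 cell count, age, exposure to TDF or protease inhibitors, etc". It then anticipates propensity score matching weights to handle the many confounders, chiefly in the time-to-albuminuria analyses.

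Two parts of Aim 2 involve HIV status as an exposure. The sample size section states "We will have approximately 80% power to detect a difference of developing albuminuria of 10% (HIV-positive) vs. 5.9% (HIV-negative", on the basis of "We will enroll 1500 (1000 HIV-positive and 500 HIV-negative) patients with normoalbuminuria and follow them for up to 30 months". The analysis plan adds, for the hypertension hypothesis, that "we will fit models with HIV status, hypertension, and an interaction between HIV status and hypertension".

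On TDF, the Aim 2 exclusion criteria remove HIV-negative people who use it for pre-exposure prophylaxis or hepatitis B. The Background describes the R3 participants as ART-experienced, "with the majority receiving TDF at some point in their course". Antiretroviral start and stop dates are collected for PWH only.

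Elsewhere the article does limit HIV-specific covariates. The Aim 1 analysis plan uses viral load only in models restricted to PWH. In Aim 2, the cumulative-TDF models are restricted to PWH, and the case–control matching uses CD4 only for HIV-positive participants.

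**The concern.** Applied as written, the rule puts three kinds of unsuitable covariate into the HIV contrast.

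- **TDF/PI exposure.** TDF is effectively zero by design in the HIV-negative group and present in most R3 participants. The two groups overlap only among TDF-naive PWH.
- **Viral suppression.** It is undefined without HIV, so the result depends on an arbitrary coding of the HIV-negative group.
- **CD4 count.** The distributions can overlap, so it need not separate the groups. The problem is that it lies downstream of HIV, and adjusting for it removes part of the effect of interest.

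ART exposure is likewise a consequence of having HIV. Table 7 is an unadjusted comparison of total incidence in the two groups. An adjusted HIV coefficient that holds ART exposure, suppression and CD4 fixed answers a different question, probably with much less information.

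**Working it through.** **Inputs.** 1000 HIV-positive and 500 HIV-negative participants; incidence p1 = 0.10 and p2 = 0.059 (Aim 2 sample size, Table 7). Two-sided alpha 0.05 is stated for Aim 1 and assumed here. The TDF-exposed share of PWH is not given beyond a majority of R3 participants, so 50% to 95% is assumed.

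**Step 1: reproduce Table 7.** Arcsine method: h = 2·asin(√0.10) − 2·asin(√0.059) = 0.6435 − 0.4907 = 0.1528. Multiply by √[1/(1/1000 + 1/500)] = 18.26 to get 2.790. Power = Φ(2.790 − 1.96) = 0.797, so the stated 80% reproduces, without adjustment. A Wald test of the log relative risk gives a lower baseline: SE = √[(1−p1)/(n1·p1) + (1−p2)/(n2·p2)] = √(0.0090 + 0.0319) = 0.202; ln(0.10/0.059) = 0.528; power = Φ(0.528/0.202 − 1.96) = 0.74.

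**Step 2: adjust an outcome model for ever-TDF.** With TDF zero in all HIV-negative participants, the HIV coefficient compares TDF-naive PWH with HIV-negative participants. The same Wald formula applies with n1 = number of TDF-naive PWH:

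| PWH ever on TDF (assumed) | TDF-naive PWH | SE(log RR) | Power, 10% vs 5.9% |
|---|---|---|---|
| 0% (no adjustment) | 1000 | 0.202 | 0.74 |
| 50% | 500 | 0.223 | 0.66 |
| 70% | 300 | 0.249 | 0.56 |
| 90% | 100 | 0.349 | 0.33 |
| 95% | 50 | 0.460 | 0.21 |

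At 100% exposed, the columns for HIV and ever-TDF coincide and the HIV effect cannot be estimated.

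**Step 3: continuous cumulative TDF.** The HIV term then stays estimable by extrapolating to zero exposure. Under an assumed gamma distribution (mean 5 years, SD 3, 90% to 100% exposed), the variance inflation factor for HIV is 1.65 to 1.94 with a linear term and 2.62 to 4.51 with a three-knot spline. With mean 8 years and all exposed, it is 3.29 and 9.93. For ever-TDF at 90% exposed it is 4.0. The precision loss is smaller than in Step 2 at the same exposure share, but the estimand is still HIV at zero TDF.

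**Step 4: matching weights from a propensity score e for HIV status.** Weights are min(e, 1−e)/e for PWH and min(e, 1−e)/(1−e) for HIV-negative participants. Every TDF-exposed PWH has e = 1 and weight 0. At 90% exposed, the other participants have e = 100/(100 + 500) = 0.167, so PWH get weight 1 and HIV-negative participants 0.167/0.833 = 0.2. The weighted comparison is about 100 versus 500 × 0.2 = 100.

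**Step 5: viral suppression.** If HIV-negative participants are coded 0, the HIV contrast rests on unsuppressed PWH, put at under 5%, so at most 50. That is the last row of the table or worse. If they are coded as suppressed, overlap is not harmed.

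**Step 6: HIV × hypertension.** In a linear outcome design with hypertension in 12.7% of PWH and 10% of HIV-negative participants (the Aim 1 figures), cell sizes are 127, 873, 50 and 450. The interaction SE, in residual SD units, is √(1/127 + 1/873 + 1/50 + 1/450) = 0.177. With ever-TDF added, and exposure assumed balanced over hypertension, it stays 0.177 at every share from 50% to 100%. The interaction is a difference of two contrasts made within HIV strata, so a covariate constant in one stratum does not remove it.

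**The case against.** The strongest defence is that this is condensed article wording. HIV-specific covariates are confined to PWH in several other places, the list ends in an open-ended abbreviation, and covariate sets for each model commonly sit in the full plan. The stated Aim 2 hypotheses concern hypertension, inflammation and TDF; none is an HIV main effect. Matching weights are only anticipated, and the exposure they would model is not named; a propensity score for hypertension would have no such overlap failure.

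Part of this stands. The propensity scenario applies only if HIV status is the modelled exposure, and the power loss is a range because the TDF share is unknown. The majority statement describes R3 participants, while Aim 2 may also include newly enrolled PWH. The defence does not remove the point, because the article states a rule covering all analyses and drops the limit it uses elsewhere, while the HIV contrast is the only one for which Aim 2 gives power.

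A reader might infer more than the documents support:

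- That the HIV effect is not identified at all. This holds strictly only if every PWH is TDF-exposed and TDF enters as ever/never, or for TDF-exposed PWH under HIV propensity weights.
- That the hypertension interaction is lost. Step 6 shows otherwise for an outcome model.
- That the plan contradicts itself by stating "Secondary analyses will exclude the anticipated small proportion (< 5%) that will not be virally suppressed" alongside enrolment of suppressed participants only. The two fit together if suppression is lost during follow-up, which a time-updated covariate would capture.

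**Conclusion.** The point holds for the adjusted HIV main effect. Followed literally, the rule replaces the total HIV effect behind Table 7 with an effect net of treatment and immune status, resting on TDF-naive PWH or on extrapolation. If ever-TDF is adjusted for and 50% to 95% of PWH are exposed, Wald power for 10% versus 5.9% falls from about 74% (80% by arcsine) to between about 66% and 21%. Continuous cumulative TDF loses less, but the estimand still changes. The exposure share is an assumption throughout.

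A separate, smaller inconsistency remains. The same part of the plan reads "All analyses will account for confounding variables, including time-updated viral suppression status (only participants with suppressed viral load will be enrolled", but the Aim 2 inclusion and exclusion criteria contain no viral load criterion.

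**What to change.** Replace the single list with two adjustment sets.

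1. **HIV-positive versus HIV-negative contrasts**, including any propensity score for HIV status: only covariates defined in both groups and not caused by HIV or ART, for example age, sex, ethnicity, smoking and BMI.
2. **PWH-only models:** add TDF/PI exposure, viral suppression and CD4, extending the restriction that Aim 1 already applies to viral load.

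Name the exposure for which each propensity score is built. Matching weights can still be used for other binary exposures such as hypertension.

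Reconcile the statement on enrolling only suppressed participants with the Aim 2 eligibility list.

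The cost is wording in the analysis plan and one eligibility reconciliation. The covariate change needs no new data and no change in sample size, and it keeps all 1000 versus 500 participants in the comparison that Table 7 describes.
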